## Abstract

**Background:**

Treating *Helicobacter pylori* is becoming increasingly difficult with the development of bacterial resistance to many established treatment regimens. As a result, researchers are constantly looking for novel and effective treatments. This trial aims to establish the efficacy of levofloxacin-based sequential treatment regimen and concomitant levofloxacin-based regimen as empirical first-line therapy in the Syrian population.

**Method:**

This is an open-label, prospective, single-center, parallel, active-controlled, superiority, randomized clinical trial. The recruitment will target *Helicobacter pylori*-positive males and females between the ages of 18 and 65 to evaluate the efficacy of empirical first-line therapy in the Syrian population. We are planning to recruit up to 300 patients which is twice the required sample size. One hundred fifty individuals will be randomly assigned to undergo either a sequential levofloxacin-based treatment regimen or a concomitant levofloxacin-based regimen. High-dose dual therapy (proton-pump inhibitor and amoxicillin) will be the rescue therapy in the event of first-line failure. The first-line eradication rate in both groups is the primary outcome, and one of the secondary outcomes is the overall eradication rate of high-dose dual therapy in the event of first-line treatment protocol failure. Intention-to-treat analysis and per-protocol analysis will be used to evaluate the eradication rates of *Helicobacter pylori* for first-line treatment protocols.

**Discussion:**

For the first time in the Syrian population, this randomized controlled trial will provide objective and accurate evidence about the efficacy of a sequential levofloxacin-based treatment regimen.

**Trial registration:**

ClinicalTrials.gov NCT06065267. Registered on October 3, 2023. Prospective registered. Enrollment of the first participant has not started yet.

**Supplementary Information:**

The online version contains supplementary material available at 10.1186/s13063-024-07906-3.

## Administrative information

Note: the numbers in curly brackets in this protocol refer to SPIRIT checklist item numbers [1]. The order of the items has been modified to group similar items [2] (see http://www.equator-network.org/reporting-guidelines/spirit-2013-statement-defining-standard-protocol-items-for-clinical-trials/).

## Introduction

### Background and rationale {6a}

Unfortunately, there is no information on the prevalence of *Helicobacter pylori* (HP) infection among Syrians [3]. A systematic review showed that the prevalence of HP infection ranges between 22 and 87.6% in Middle Eastern countries; regrettably, it did not include any data from Syria [4]. Syrian refugees may have an HP infection prevalence similar to that of their native country. There are two reports of the prevalence of HP infection among Syrian refugees. The first reported that only 8 individuals (66.7%) from the Middle East region were infected with HP when they presented to a family care clinic in the USA. Unfortunately, this prevalence includes patients from across the Middle East and may not adequately reflect the prevalence of infection among Syrians [5]. The second report from Germany revealed that the prevalence of HP infection among Syrian refugees was about 34%, which may be closest to reality [6]. The prevalence of HP infection appears to be higher in developing nations than in industrialized nations, with the majority of infections happening during childhood. Poor sanitation standards, low-income levels, and overcrowded living conditions appear to be associated with a higher prevalence of HP infection [7]. The recent humanitarian crisis has had a terrible impact on Syrian lives, resulting in millions of refugees and displaced individuals, massive infrastructure destruction, and the greatest economic catastrophe Syria has ever faced. It had an enormous impact on the health sector, with up to 50% of health facilities destroyed and up to 70% of healthcare providers fleeing Syria [8, 9]. Peptic ulcer disease and consequent bleeding [10–12], gastric adenocarcinoma [13, 14], dyspepsia [15, 16], mucosa-associated lymphoid tissue (MALT) lymphoma [17, 18], unexplained iron deficiency anemia [19], and idiopathic thrombocytopenic purpura [20, 21] are all linked to HP infection, which requires antimicrobial treatment [22, 23]. In real-world applications, only a few antibiotics are efficient at eradicating HP infection. Treatment regimens include a combination of two or three antibiotics, and a proton pump inhibitor (PPI), with or without a bismuth component that gives extra antibiotic properties [22, 23]. However, the increasing antibiotic resistance of HP has become a major global problem [24–35]. In Syria, the eradication rate of traditional triple therapy with clarithromycin or levofloxacin was less than 30% [36], whereas the eradication rate with the levofloxacin concomitant regimen and the doxycycline-bismuth-based quadruple regiment was 82.05% and 78.9%, respectively [37]. As a result, there is a need to look for more effective therapeutic regimens as well as the best therapeutic regimens for follow-up when the first line of treatment fails.

## Objectives {7}

The main objective of this study is to compare the eradication rate of HP infection using levofloxacin-based sequential therapy against levofloxacin-based concomitant therapy using an intention-to-treat analysis (ITT) and a per-protocol analysis (PPA).

## Trial design {8}

This is a single-center, prospective, superiority randomized, open-label, active-controlled clinical trial with a 1:1 allocation ratio. Figure 1 shows a trial flow chart.

**Fig. 1 Fig1:**
[figure not shown]
Trial flowchart

## Methods: participants, interventions, and outcomes

### Study setting {9}

The research will be carried out in Damascus Hospital’s outpatient clinic. Damascus Hospital is the primary medical facility affiliated with the Ministry of Health. Damascus, Syria’s capital, treats patients from throughout the country.

### Eligibility criteria {10}

#### Inclusion criteria

(1) Men and women between the ages of 18 and 65 years; (2) naive to HP infection treatment; (3) HP-positive, as determined by histological examination.

#### Exclusion criteria

(1) Allergic to any medicine supplied; (2) pregnant or lactating; (3) suffering from serious systemic disorders, such as severe cardiopulmonary or hepatic dysfunction; (4) having had a previous gastrectomy or a history of stomach cancer; (5) chronic renal failure; (6) unwilling to participate in the trial; (7) persistent use of non-steroidal anti-inflammatory drugs (NSAIDs), antibiotics, proton-pump inhibitors (PPIs), H_2_ receptor antagonists, aspirin, herbal remedies, and probiotics during the trial procedure. Keeping to take any dose of any previous medication is compatible with the concept of persistence, and any participant who also starts using or uses any of these treatments during the trial or follow-up will be excluded [38].

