### Sample size {14}

We will conduct this as a superiority clinical trial, and the calculation of the sample size is based on the primary outcome, which is the eradication rate of HP infection using ITT. According to a meta-analysis, Kale-Pradhan et al. reported the eradication rate of a sequential levofloxacin-based treatment regimen as 87.8% (P2 = 0.877) [40], while the eradication rate of a concomitant levofloxacin-based regimen was based on the results of a randomized clinical trial conducted in Syria and was 82.05% (P1 = 0.8205) [37]. We applied the following statistical hypotheses: (1) 80% power (*β* = 0.2); (2) the 5% level of significance (*α* = 0.05); and (3) the superiority margin is 10% (*δ* =  − 0.10) and (*ε* = 0.20). Given that *Zα* and *Z*_*β*_ are 1.64 and 0.845, respectively; (4) the ratio of case to control is equal to one (*K* = 1). The sample size formula of the two parallel superiority designs resulted in 64 patients as a sample size for each parallel [47, 48]. We also added 15% for possible dropouts, making the final sample size 150 patients. For more information, please check Additional file 1.

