## Data collection and management

### Plans for assessment and collection of outcomes {18a}

During screening, sociodemographic and baseline information (including age, sex, contact information, and past medical history) will be obtained. The success of HP eradication will be assessed by stool antigen assays performed with the enzyme immunoassay method (EIA) 6 weeks following the completion of therapy [45]. Participants will be prohibited from using PPIs, antibiotics, H_2_ receptor antagonists, aspirin, herbal remedies, and probiotics for 8 weeks until the stool antigen testing. The stool antigen tests must be performed no later than 6 weeks + 3 days after the completion of therapy. The data on adverse events and compliance will be obtained face-to-face and documented using the data collection form no later than 3 days following the completion of therapy. The count of pills taken will be used to determine study drug compliance. The data will be obtained from two trained assistants who are instructed to collect the information in a consistent, reproducible manner, and the integrity of the data will be overseen by the principal investigator.

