## Statistical methods

### Statistical methods for primary and secondary outcomes {20a}

To compare the eradication rate of HP, we will use the ITT analysis (all individuals who got at least one dosage of the trial treatment) and PPA (all individuals who complied and were tested again using a stool antigen test). We will use the *χ*^2^ test, which will be used for nominal variables, such as sex, treatment protocol, treatment outcome based on stool antigen tests, each adverse event, smoking, and alcoholic status, to determine if there is a relationship between the treatment protocol and the result of the treatment for both the primary and secondary outcomes [50]. We will use the *t*-test to compare the means of the continuous variable, such as patient’s age, with the normal distribution for both the primary and secondary outcomes [51]. The difference in eradication rates between the two treatment regimen groups can be assessed by a two-sided 95% confidence interval (CI). Individuals whose stool antigen tests have not been retested including dropouts will be considered treatment failures. The statistical significance level is a *P*-value of 0.05.

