## Discussion

The prevalence of HP infection in Syria is high and is estimated to be about 34% [6]. On the other hand, 67.3% of the Syrian population practiced self-medication, while the most commonly used drugs were antibiotics, which create another problem related to bacterial resistance [52]. Antibiotic resistance restricts the efficacy of triple therapy for HP infections around the world, necessitating searching for new treatment protocols. Until 2018, the most commonly used HP treatment in Syria was triple therapy with clarithromycin and, to a lesser extent, triple therapy with levofloxacin, until a pilot trial was conducted in Syria and proved the ineffectiveness of these regimens [36]. Treatment guidelines recommend the use of levofloxacin-concomitant or bismuth-containing regimens as an alternative first-line treatment, particularly in areas with a high frequency of clarithromycin resistance like Syria [22, 23]. Knowing that levofloxacin concomitant, or levofloxacin sequential, and bismuth-based protocols are the most commonly used for HP infection in Syria. Unfortunately, neither treatment regimen was as effective as expected, since in Syria, the HP eradication rate did not exceed 82% at best [37, 53]. A meta-analysis revealed that a fluoroquinolone-based sequential regimen is a viable therapeutic option for HP infection treatment, with an eradication rate of 87.8%, but it was not evaluated in Syria [40]. As a result, it was critical to find a treatment regimen with a higher eradication rate, and the most important thing was to estimate the eradication rates of a rescue regimen with dual therapy with high-dose PPI and amoxicillin following the failure of the first line [22]. In general, compliance with medication is defined as adherence to taking over eighty percent of prescribed medications. Despite the fact that this regimen is believed to be beneficial, there are concerns about compliance because of the medication change between the first and second weeks [38]. This study will evaluate the two HP treatment regimens that are now of the most interest. Furthermore, because Damascus Hospital is the main hospital linked with the Ministry of Health, we will enroll patients from all throughout Syria. A suitable sample size will be collected to address the trial question statistically. This trial will generate critical evidence that will lead to adjustments in first-line treatment regimens for *Helicobacter pylori* infection in Syria, thus increasing eradication rates and enhancing patient life quality.

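### Randomised patients who later take a restricted drug are to be excluded, but the protocol does not say from what, so their place in the ITT primary analysis is unsettled

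*Protocol article*

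**What the plan says.** The seventh item under Exclusion criteria covers persistent use of NSAIDs, antibiotics, PPIs, H2 antagonists, aspirin, herbal remedies and probiotics. The threshold is low: "Keeping to take any dose of any previous medication is compatible with the concept of persistence". The item then reaches past baseline: "any participant who also starts using or uses any of these treatments during the trial or follow-up will be excluded".

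The primary outcome is described in Sample size {14} as one "which is the eradication rate of HP infection using ITT". Statistical methods {20a} defines the two sets:

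- "ITT analysis (all individuals who got at least one dosage of the trial treatment"
- "PPA (all individuals who complied and were tested again using a stool antigen test"

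The same section adds: "Individuals whose stool antigen tests have not been retested including dropouts will be considered treatment failures".

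Section {11d} restricts these drugs during the trial. Section {18a} prohibits most of them "for 8 weeks until the stool antigen testing". Neither says how a patient who breaks the rule is analysed. Sections {20b} and {20c}, on additional analyses, non-adherence and missing data, do not say either.

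**The concern.** Starting a drug during treatment or follow-up can be observed only after enrolment, so the rule acts on patients who have been randomised and usually dosed. The event may also be related to the result or the regimen. Acid suppressants or NSAIDs could be taken for persisting symptoms. They could also be taken for adverse effects, and {11b} lists abdominal pain and nausea among the common ones. The two regimens differ and participants know which one they receive, so use could differ by arm.

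At stake is who enters the primary analysis and how they are scored. If users are dropped, the comparison is no longer between the groups as randomised. If they are withdrawn untested, some cured patients are recorded as failures. The protocol as written does not settle which of these happens.

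**Working it through.** **1. The passages side by side.** Take a patient who has one dose of trial treatment and later takes one aspirin. Exclusion criteria says this patient is excluded; {20a} places the same patient in ITT. There are three possible readings.

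| Meaning of excluded | Fate in the primary analysis | Fit with {20a} |
|---|---|---|
| Removed from the trial and its analyses | Leaves numerator and denominator | Conflicts with the ITT definition |
| Withdrawn from the trial | Untested, counted as failure | Consistent, but an obtainable result is given up |
| Left out of per-protocol only | Stays in ITT | Consistent, but stated nowhere |

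The sentence stands without limitation among the eligibility criteria, so the first reading is the plain one.

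**2. The plan's figures.** From Sample size {14}: P1 = 0.8205 (concomitant) and P2 = 0.877 (sequential). The planned difference is 87.70 − 82.05 = 5.65 points. The stated 64 per arm reproduces with the plan's own inputs:

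(1.64 + 0.845)² × [0.8205 × 0.1795 + 0.877 × 0.123] / (0.0565 + 0.10)² = 6.1752 × 0.25515 / 0.024492 = 64.3.

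The point does not depend on that figure.

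**3. Exclusion related to outcome (assumed rates).** Let a be the share of cured and b the share of failed patients who are excluded. The observed rate is p′ = p(1 − a) / [p(1 − a) + (1 − p)(1 − b)].

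| a, b | Concomitant | Sequential | Difference |
|---|---|---|---|
| 10%, 20% | 0.73845/0.88205 = 83.72% | 0.7893/0.8877 = 88.92% | 5.2 |
| 10%, 30% | 0.73845/0.86410 = 85.46% | 0.7893/0.8754 = 90.16% | 4.7 |

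The denominators show that about 11–14% of patients would be excluded. With the same pattern in both arms, the difference shrinks by about 0.5 to 0.9 points.

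**4. The same pattern in one arm only.**

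- Sequential only: 88.92 − 87.70 = 1.2 and 90.16 − 87.70 = 2.5 points, which raises the difference.
- Concomitant only: 83.72 − 82.05 = 1.7 and 85.46 − 82.05 = 3.4 points, which lowers it.

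The bias is therefore 1.2–3.4 points, in either direction.

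**5. Use unrelated to outcome, 10% in both arms (assumed).**

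- Users dropped: both rates are unchanged and the difference is 5.65.
- Users counted as failures: 0.877 × 0.9 − 0.8205 × 0.9 = 78.93% − 73.85% = about 5.1 points.

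**The case against.** The strongest reply is that this is an ambiguity, not a contradiction. Section {20a} never mentions restricted-drug users, and the exclusion sentence never mentions the analysis. A user who is withdrawn, goes untested, counts as a failure in ITT and is absent from the per-protocol set satisfies both. This stands, so a reader who infers that the two rules cannot both be followed goes too far. It does not remove the problem. Nothing in the protocol selects that reading, and under it a patient who could have been tested is scored as a failure because of a drug taken after randomisation.

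Four other inferences are tempting and not supported:

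- **That the ambiguity is worth more than the whole planned effect.** With 10% use, one arm's rate moves from 82.05% to 73.85%, about 8.2 points. That is a change in an arm's level, not in the difference between arms. The same use in both arms moves the difference only from 5.65 to about 5.1.
- **That restricted-drug use will be common.** The Discussion says "67.3% of the Syrian population practiced self-medication". This describes the general population, not participants told to avoid these drugs and contacted twice a week. It cannot support the assumed 10–30%.
- **That exclusion selectively removes failures.** This is plausible, but no document figure shows it.
- **That the rule would be chosen to suit the result.** Under {17a}, laboratory staff, data collectors and data analysts stay blinded. Participants and researchers do not, so the risk is reduced rather than absent.

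It can also be said that such handling belongs in a statistical analysis plan that is not shown. That would answer a silence. Here the article itself states an unqualified exclusion beside an ITT definition with no exception for it.

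**Conclusion.** The point holds as a defect that should be fixed. The protocol excludes patients on a post-randomisation event that may be related to outcome or regimen, does not say from what, and bases its primary outcome on ITT. The plain reading conflicts with ITT; the withdrawal reading fits the wording of {20a} but records failures that may not be failures.

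The size cannot be derived from the documents, because they give no rate of restricted-drug use. Under the assumed rates, the effect on the planned 5.65-point difference is modest when use is alike in both arms (about 4.7–5.2 points after outcome-related exclusion; about 5.1 if users unrelated to outcome are scored as failures). The bias is 1.2–3.4 points if outcome-related exclusion occurs in one arm only. Dropping users causes no bias if they eradicate at the same rate as other patients in their arm. The documents do not show that use will differ by arm, or that the trial's conclusion would change.

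**What to change.** Reconcile Exclusion criteria with {20a}:

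- Make criterion 7 a baseline eligibility criterion only. The restriction on these drugs during the trial can remain as it is.
- State that later restricted-drug use is a recorded protocol deviation. These patients still have the 6-week stool antigen test, stay in ITT in their allocated arm, and are removed only from the per-protocol set.
- Pre-specify one ITT outcome rule for a test taken under such use, either the observed result or not eradicated, and use the other as a sensitivity analysis. Either order can be defended; what matters is that it is fixed beforehand.
- Report the frequency of restricted-drug use by arm.

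The cost is a sentence in each of the two sections and one extra analysis. The downside is that some ITT results will come from tests taken under restricted drugs, which the sensitivity analysis addresses. Trial status says that no patient had been enrolled at version V3, so at that version the rule could be settled before any outcome data existed.

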### Who will take informed consent? {26a}

Before beginning any trial procedures, investigators must get written informed consent from patients. The investigators will explain and discuss the experiment with potential volunteers to ensure that they understand what is being studied and that their involvement is entirely voluntary. Patients will be informed that they can drop out of the trial at any time. It was explicitly specified that only clinical information would be discussed in the research, with no private data mentioned in any part of the trial report. It was made clear to all patients that dropping out of the trial would not affect the quality of follow-up or treatment.

### Additional consent provisions for collection and use of participant data and biological specimens {26b}

A written request form must accompany every specimen, and the identification information on the specimen and requisition must be identical. The requisition form must contain all the following information: (1) patient’s legal name, (2) unique identification number, (3) age, (4) source of the specimen, (5) complete provider details, (6) underlying medical condition, and (7) pathology investigations requested. All specimen containers must be leak-proof, placed in a secondary leak-proof container for transport to the laboratory, and transported to the laboratory as quickly as possible. Tissue specimens must be suspended or totally immersed in ten times their volume of 10% neutral-buffered formalin to maintain the integrity of the specimen. The initial informed consent form contains data collection and request information.

### Interventions

#### Explanation for the choice of comparators {6b}

For two weeks, patients on the concomitant levofloxacin regimen will receive levofloxacin 500 mg once daily, amoxicillin 1000 mg, tinidazole 500 mg, and esomeprazole 20 mg twice daily. When applied as a first-line treatment, the previous regimen had the highest eradication rate for Syrian patients naive to HP treatment [36, 37]. A rescue regimen of high-dose dual therapy consisting of esomeprazole (40 mg twice daily) and amoxicillin (1000 mg three times daily) for 2 weeks will be used after first-line treatment fails [22, 39].

#### Intervention description {11a}

The sequential levofloxacin regimen consists of esomeprazole 20 mg and amoxicillin 1000 mg taken twice daily for 1 week, followed by metronidazole 500 mg, esomeprazole 20 mg twice daily, and levofloxacin 500 mg once daily for 1 week [22, 40]. Microscopic examination of the stomach biopsies and hematoxylin and eosin, followed by Giemsa stains [41], will be used to confirm HP infection, which has a sensitivity and a specificity of 95% and 99%, respectively [41]. Gastric biopsies will be collected via gastroduodenoscopy and forwarded to the pathology laboratory of the same referral hospital. According to the Sydney system [42], endoscopists obtained five stomach biopsies: two from the body, two from the antrum, and one from the incisura. If the first-line treatment fails, a high-dose dual therapy of PPI and amoxicillin will be provided as a rescue therapy [22].

